# Efficacy of tibolone and raloxifene for the maintenance of skeletal muscle strength, bone mineral density, balance, body composition, cognitive function, mood/depression, anxiety and quality of life/well-being in late postmenopausal women ≥ 70 years: Study design of a randomized, double-blind, double-dummy, placebo-controlled, single-center trial

**DOI:** 10.1186/1745-6215-9-32

**Published:** 2008-06-05

## Abstract

**Background:**

Postmenopausal women are prone to develop functional disabilities as a result of reduction in muscle strength and muscle mass caused by diminished levels of female sex hormones. While hormone replacement therapy may counteract these changes, conventional hormone replacement therapy is associated with potential harmful effects, such as an increased risk of breast cancer, and its prescription is not recommended. For this reason newer alternative drugs, such as tibolone, a synthetic steroid with estrogenic, progestogenic and androgenic activity, and raloxifene, a selective estrogen receptor modulator, may be more appropriate. This trial investigates the effect of tibolone and raloxifene on muscle strength.

**Methods:**

We recruited 318 elderly women in our single-center randomized, double-blind, double-dummy, placebo-controlled trial. Participants were randomized to tibolone 1.25 mg (Org OD 14, Organon NV, the Netherlands) plus placebo, raloxifene 60 mg (Evista^®^, Eli Lilly, United States) plus placebo or two placebo tablets daily for 24 months.

The primary aim is to determine if there is a difference between tibolone and placebo or if there is a difference between raloxifene and placebo. Primary endpoints are muscle strength and bone mineral density. The secondary endpoints are postural balance, body composition, cognitive function, anxiety, mood and quality of life. The secondary aim is to determine if there is a difference between tibolone and raloxifene.

The measure of effect is the change from the baseline visit to the visits after 3 months, 6 months, 12 months, and 24 months. A follow-up measurement is planned at 30 months to determine whether any effects are sustained after cessation of the study. By December 2007 the blind will be broken and the data analyzed.

**Trial registration number:**

NTR: 1232

## Background

Aging is associated with muscle atrophy, physical frailty, and impaired cognitive function. This functional decline can severely affect quality of life and reduce the likelihood of a person being able to live independently. Women are more vulnerable to the effects of this age-related muscle loss because their peak muscle mass is lower than that of men and around the time of menopause they experience an additional 15% loss of muscle mass [1-3]. Hormonal replacement therapy (HRT) in postmenopausal women may prevent muscle strength decline [2,4-9]. Unfortunately, however conventional hormone replacement therapy has serious side-effects such as an increased risk of breast cancer, thrombo-embolism, cholecystitis, stroke and coronary events, especially in elderly women. Unopposed estrogen replacement therapy increases the risk of endometrial carcinoma. [10,11]

For this reason, newer drugs, such as tibolone, a synthetic steroid with oestrogenic, progestogenic, and androgenic activity, and raloxifene, a selective estrogen receptor modulator, may be more attractive.

Tibolone is a tissue-specific compound that has favorable effects on bone, vagina, climacteric symptoms, mood, and sexual well-being in postmenopausal women, without having an estrogen-like stimulating effect on the endometrium or breast [12]. In a randomized, placebo-controlled and double-blind trial involving early postmenopausal women, handgrip strength increased by about 4% after 1 year of treatment with tibolone 2.5 mg [13]. Tibolone 1.25 mg may be effective in preventing osteoporosis and post-menopausal symptoms.

Selective estrogen receptor modulators (SERMs) are a diverse group of compounds that bind with specificity and high affinity to estrogen receptors (ER) consisting of the ER α and the ER β. SERMs can act as either ER agonists or antagonists, depending on the tissue type. Raloxifene hydrochloride is a nonsteroidal benzothiophene with estrogen agonistic effects on bone, serum lipids, and the arterial vasculature and with estrogen antagonistic effects in the breast and uterus [14]. Raloxifene has been approved for osteoporosis prevention and the treatment of postmenopausal osteoporosis in several countries. Its actions on bone are similar to those of estrogens [15].

Relatively little is known about the effects of estrogen supplementation, with regard to frailty, initiated later in the postmenopausal period (> 70 years) and even less is known about the effects of tibolone and raloxifene on muscle strength, body composition, bone mineral density (BMD), balance, cognitive function and mood/depression in late postmenopausal women. The purpose of this study is to determine whether these newer drugs have beneficial effects in older postmenopausal women.

## Design and Methods

The study is a single-center, randomized, double-blind, double-dummy, placebo-controlled trial to evaluate the effect of tibolone and raloxifene on skeletal muscle strength, body composition, BMD, balance, cognitive function, mood/depression, anxiety and quality of life in late postmenopausal women aged ≥ 70 years. The aim was to recruit 325 study subjects, so that, after allowing for a drop out rate of 30 % over 2 years, data could be collected from 225 women.

Participants were randomly assigned by the hospital pharmacy of the University Medical Center of Utrecht using computerprogramm "Design" to one of the three treatment groups in a 1:1:1 ratio after baseline measurements had been taken. The sub-blocks contained 12 numbers. The design is double-blind. We do not expect that unblinding by symptoms will occur. In a diary we actively inquired about leg cramps and flushing. These have been reported to be side effects of raloxifene, but only in 0–10% for legcramps and more than 10% for flushing [16]. Legcramps also occur often in women of this age.

The treatment period was 24 months, with 1 month being considered to be 28 days. Assessments were performed at baseline and after 3, 6, 12, and 24 months. Participants will also be assessed at 30 months, to determine whether treatment has a lasting effect. The Institutional Review Board of the University of Medical Center Utrecht approved the study protocol. All participants gave written informed consent at the screening visit.

### Inclusion criteria

-Healthy postmenopausal women;

-Minimum age 70 years at the time of inclusion;

-Body mass index between 18 and 35 kg/m^2^,

-Subjects should be willing and able to comply with the protocol for the duration of the study, after written informed consent.

### Exclusion criteria

-Steroid therapy or other drugs affecting muscle mass taken during the last 6 months;

-History or presence of any malignancy (except non-melanoma skin cancers);

-Undiagnosed abnormal vaginal bleeding in the past year prior to screening;

-Presence or history of endometrial hyperplasia with or without atypia;

-Presence or history of cardiovascular, cerebrovascular or thrombo-embolic disorders;

-Current liver or renal disease or history of this condition;

-Uncontrolled hypertension (systolic blood pressure ≥ 170 mm Hg systolic and/or diastolic blood pressure ≥ 105 mm Hg);

-Osteoporosis: Z-score < -2

-Bone disease other than osteoporosis such as Paget's disease;

-Osteomalacia or bone metastases;

-Alcohol abuse (average intake of more than 4 alcohol containing units per day);

-Smoking more than 10 cigarettes/day;

-Use of sex hormones, corticosteroids, insulin, anti-coagulants or enzyme-inducing drugs;

-Treatment with tibolone or raloxifene within the last 6 months;

-Known hypersensitivity to tibolone or raloxifene;

-Presence of any condition, concomitant disease, intercurrent illness or resultant therapy that would interfere either with the participants' compliance or with the results of the study and/or their evaluation;

-Major problems with locomotion and cognitive impairment (MMSE < 24);

-Participation in another study.

### Recruitment

Recruitment started on 23 July 2003 by means of an advertisement placed in the local newspaper (reaching 194.000 households, only a few involving women 70 years or older). Interest in the study was expressed by 80 women; 38 women were randomized. Further recruitment was done by mailing 16.090 women aged 70–80 years whose addresses were selected by the municipal register of the cities Utrecht, Zeist, Houten, Bilthoven, and Driebergen. Women who previously participated in research at the geriatric department were also recruited (table 1).

**Table 1 T1:** Recruitment, inclusion and exclusion.

**Recruitment**	**Total**	**Positive response**	**Exclusion after positive reaction**	**Exclusion after screening**	**Inclusion**	**Never started**
Local newspaper:	unknown	80	38	4	38	6
UMC group	172	32	8	8	16	3
Local municipal registers	16090	541	249	28	264	26

total	16262	653	295	40	318	35

Women were asked to complete a questionnaire about the type of medication used, number of falls, troubles walking, use of a walking aid, dyspnea, history of thrombosis, liver complaints, hysterectomy or uterine complaints, weight, and height. Women who did not meet the inclusion criteria were sent a letter thanking them for their interest. Those who met the inclusion criteria and who were still interested in participation were invited, by telephone, to a screening visit. During this telephone conversation, the participant's medical history was checked for exclusion criteria.

Two hundred and seven women were excluded and 87 women refused to participate or there were other reasons for exclusion. Reasons for exclusion after a positive reaction and after screening are given in table 2 and 3. A flow chart of study recruitment is given in figure 1.

**Table 2 T2:** Reasons for exclusion after positive response

**Exclusion reason:**	**Total:**
Subject does not want to	79
Already involved in another study	2
BMI > 33 or < 18	28
Cardiovascular disease	42
Hypertension	3
Thrombo-embolic disease	33
Malignancy	26
COPD	1
Liver problem	2
Decreased functionalability	3
On hormone replacement therapy	22
Contra-indicated medication	46
Parkinsonism	1
Osteoporosis	1
Two-sided hip prothesis	5
Moved to Spain/Belgium	2
General practitioner advised not to participate	1

Total	294

**Table 3 T3:** Exclusion after screening.

**Exclusion reason:**	**Number:**
Malignancy	3
Benign abnormality	4
Medication	4
Hypertension	4
BMI > 35	2
Angina pectoris	4
TIA	1
Thrombosis	2
Untreated diabetes mellitus	1
Surgery	1
Own reasons	9
MMSE < 24	3
Skin problems	1
Pain/functional disability	1

total	40

**Figure 1 F1:**
[figure not shown]
**Flowchart representing recruitment after a newspaper advertisement and after invitation of women ≥ 70 years selected by municipal registers of several cities and women who participated before in a study of the geriatric department. **Suitable women were invited for a screening visit. They were included in the trial if they met the inclusion criteria and after written informed consent. Then randomization took place.

### Information and screening

At the screening visit women were informed about the trial and gave their written informed consent. A medical and gynecological history was obtained and medication use was recorded. Blood pressure, heart rate, weight, and height were measured and mamma palpation, cardial, pulmonal and abdominal examinations were performed. In- and exclusion criteria were checked again using a list of questions. Finally, a Mini Mental State Examination was performed. Forty women were excluded after screening (table 3). Within 28 days of the screening visit, baseline measurements were taken and the participants were randomized.

### Randomization visit and baseline assessments

Baseline measurements were taken within 28 days of screening at the time of randomization. Mammography was performed in all women except those who had had a mammography within 12 months before randomization. If there was an abnormality, malignancy or dubious malignancy, the participant was excluded. Dual Energy X-ray Absorptiometry (DEXA) was performed to measure BMD. If the z-score was lower than -2, the subject was excluded; if the z-score was between -1 and -2, the subject was given calcium supplements and entered the trial.

At baseline muscle strength and power were measured and functional mobility was assessed with the timed "up and go test". Postural balance was determined with body sway and functional reach. Women completed the Women's Health Questionnaire (WHQ) to determine quality of life. Other questionnaires administered were on habitual physical activity (HPA), the State Trait Anxiety Inventory (STAI) and the Geriatric Depression Scale. Cognitive function was determined with a 15 word test and a trail B test. The tests used at successive visits are given in table 4.

**Table 4 T4:** Examinations and assessments.

Assessment	Visit 1	Visit 2	Visit 3	Visit 4	Visit 5	Visit 6	Visit 7
	screen	Base	mnth3	mnth6	mnth12	mnth24	mnth30
Medical history	X						
Physical examination	X						
Gynaecologicol examination	X						
Breast examination	X						
Mammography*	X						
In/exclusion criteria	X						
Vital signs	X	X	X	X	X	X	X
Bone mineral density		X				X	
Body composition		X	X	X	X	X	X
Muscle strength		X	X	X	X	X	X
Cognitive function		X	X	X	X	X	X
Functional mobility		X	X	X	X	X	X
Mood/depression		X	X	X	X	X	X
Quality of life		X	X	X	X	X	X
HPA		X	X	X	X	X	X
Adverse events			X	X	X	X	
Drug accountability			X	X	X	X	

* Only if not performed in the year before.

Randomization started at July 15^th ^2003. Three hundred and eighteen women were randomized. Thirty-five women were excluded after randomization because of osteoporosis (n = 13), mamma carcinoma or abnormality on mammography (n = 6), hypertension (n = 1), polymyalgia rheumatica (n = 1) and some women decided to withdraw from the study at this stage (n = 14). Participants were randomized to receive tibolone 1.25 mg (Org OD 14, Organon NV, the Netherlands) plus placebo, raloxifene 60 mg (Evista^®^, Eli Lilly, United States) plus placebo or two placebo tablets daily for 24 months. Because the results of the Long term Intervention on Fractures with Tibolone (LIFT)-study suggested there was a higher risk of cerebrovascular accidents with tibolone use after an average of 2.4 years (hazard ratio 2.3), our research group decided to stop the tibolone arm of the study on February 2006 [17]. One hundred and five women were randomized to use tibolone. Of those women 15 never started the study, 27 already dropped out 15 after baseline, 5 after 3 months, 3 after six months, 4 after one year measurements), and 19 women had to stop the study before one year measurements were reached. Available one-year data about the tibolone group (n = 44) will be analysed.

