### Power calculation

Changes in muscle strength and BMD are the primary endpoints to judge the efficacy of supplementation with both study drugs. In order to demonstrate a between-group difference in handgrip strength of at least 3.6% and a difference in BMD of at least 2.6%, a power calculation indicated 75 subjects per group completing the study. To allow for drop-out and protocol violations, it was calculated that 324 subjects would need to be recruited, 108 in each intervention arm. This number is based on conventional assumptions of alpha = 0.05 and beta = 0.2 and a drop-out of 30%. Mean and SD for handgrip strength were taken from our previous study on the effect of tibolone in postmenopausal women [13].

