### Data analysis

#### Efficacy

Analysis will be done concerning tibolone versus placebo and raloxifene versus placebo. If both show a significant beneficial effect, the difference between tibolone and raloxifene will be analysed. However, this is not expected. After termination of the Tibolone-arm during our study, our concern is that the tibolone-placebo comparison will be underpowered. Analyses will be done with 3 months, 6 months en 12 months (n = 44) data to determine whether there is a treatment effect of tibolone. In previous studies with a comparable number of participants or fewer, a significant beneficial effect was reported on body composition after 1 year of treatment [43,44], so we might find an effect as well.

The efficacy analysis will be based on the intention to treat group (ITT), all subjects of the treated group who had at least one post baseline assessment of at least one of the primary outcome variables. In addition a per-protocol (PP) analysis will be performed, using data for all subjects from ITT group without any major protocol violation. Differences between the ITT and PP results will be examined.

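### The one-year tibolone sample of 44 does not match the article's own flow, which gives 48 women measured at one year

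*Protocol article*

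**What the plan says.** The section Randomization visit and baseline assessments gives the flow of the tibolone arm up to its closure in February 2006:

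- Allocation: "One hundred and five women were randomized to use tibolone".
- Non-starters: "Of those women 15 never started the study".
- Drop-outs by timing: "27 already dropped out 15 after baseline, 5 after 3 months, 3 after six months, 4 after one year measurements".
- Women cut off by the closure: "19 women had to stop the study before one year measurements were reached".
- Resulting sample: "Available one-year data about the tibolone group (n = 44) will be analysed".

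The Efficacy section carries the figure into the analysis: "Analyses will be done with 3 months, 6 months en 12 months (n = 44) data". It also defines the intention-to-treat group as "all subjects of the treated group who had at least one post baseline assessment of at least one of the primary outcome variables". Table 4 schedules muscle strength, a primary endpoint, at month 12. Bone mineral density is scheduled only at baseline and month 24.

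**The concern.** The drop-out list names, for each group, the last assessment point before leaving. Read that way, the four women in its last item had their one-year visit and then left. They should therefore count among women with one-year data, but 44 can be reached only by taking them out. It looks like the number still in the study after the one-year visit, presented as the number with one-year data.

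If 44 is just a miscount, the article misstates the sample for a planned comparison. If 44 is the set that will be analysed at 12 months, four women with an observed outcome would be left out because they later dropped out. That selects on an event after the outcome and conflicts with the intention-to-treat definition. The tibolone-placebo comparison can least afford to lose data, since the article already fears that it is underpowered.

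**Working it through.** **Inputs** (section Randomization visit and baseline assessments): 105 randomised to tibolone; 15 never started; 27 drop-outs, split 15, 5, 3 and 4; 19 stopped before the one-year visit.

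**1. Does the drop-out list add up?** 15 + 5 + 3 + 4 = 27. Yes.

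**2. Reproduce the stated figure.** Randomised, minus non-starters, minus all drop-outs, minus those stopped early:

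105 - 15 - 27 - 19 = 44.

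This matches exactly, so the four who left after the one-year measurements have been subtracted.

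**3. Count women who reached the one-year measurement.** Subtract only losses before that visit:

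105 - 15 - (15 + 5 + 3) - 19 = 105 - 15 - 23 - 19 = 48.

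**4. Try another reading.** Suppose the 15 non-starters and the 15 who left after baseline are the same women. Then 105 - 27 - 19 = 59, or 105 - 23 - 19 = 63 if the four are kept. Neither gives 44, so this overlap does not explain the figure.

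**5. Size in outcomes.** 48 - 44 = 4 women; 4/48 = 8.3%.

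**6. Size in power (illustration).** The Power calculation section says that "a power calculation indicated 75 subjects per group completing the study", with two-sided alpha taken as 0.05 and beta 0.2. It does not print the standard deviation, so the standardised difference is backed out from the 75 per group:

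d = (1.960 + 0.842) × √(2/75) = 0.457.

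With n tibolone women and m placebo women, power ≈ Φ(d / √(1/n + 1/m) - 1.960). The article gives no placebo number at one year, so m is an assumption:

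| Assumed placebo women | Tibolone n = 44 | Tibolone n = 48 |
|---|---|---|
| 75 (planned completers) | 67% | 70% |
| same as the tibolone arm | 57% | 61% |

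The four women are worth about 2 to 4 percentage points of power.

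**7. Set against the intention-to-treat rule.** A treated woman with a muscle-strength measurement at any post-baseline visit belongs to the group. A woman who left only after the one-year measurements meets that condition if her muscle strength was measured. Nothing in the definition removes her for leaving later.

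**The case against.** Four points can be made on the other side.

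*The count of 48 is not established.* The source sentence is loosely worded and lacks an opening bracket. The four might have no usable one-year measurement, or might have been removed under the rule in Compliance monitoring that excludes women who missed too much trial medication. This stands as a limit: 48 is what the printed flow implies, and only the database can confirm it. However, the article gives no such reason for these four. An exclusion for non-compliance would also more naturally define the per-protocol set than the intention-to-treat set.

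*No exclusion rule is written down.* A reader might infer that the plan discards outcomes of women who later drop out. The article does not say so. It gives a count, and its only stated rule would include the four. The charge of selection is therefore conditional on 44 being the set actually analysed.

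*The figure may be read too widely.* A reader might take 44 as the sample for the 3- and 6-month analyses too, since all three visits stand in one sentence of the Efficacy section. The bracket directly follows the 12-month item, and the other place ties 44 to one-year data. Nothing limits the earlier analyses to 44 women.

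*The consequence is small.* This stands. The arm was already closed, and the article concedes low power for this comparison. The raloxifene-placebo comparison and the planned sample size are untouched.

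**Conclusion.** The discrepancy is real but minor. The article's own flow gives 48 women measured at one year on tibolone. The stated 44 is reached only by subtracting four women who left after that measurement. This rests on the plain reading of the drop-out list, in which each item names the last visit completed.

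The figure is therefore either wrong as a count of available one-year data, or right as an analysis set that departs from the intention-to-treat definition without a stated reason. The documents do not show which. The stake is four women in one comparison; the power figures that express it depend on the assumed placebo numbers. The reason to correct it is consistency between the flow, the stated sample and the intention-to-treat rule, rather than any material gain in power.

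**What to change.** Check in the database whether the four women who left after the one-year visit have a muscle-strength measurement at month 12.

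- If they do, change 44 to 48 in Randomization visit and baseline assessments and in Efficacy, and include the four in the 12-month intention-to-treat analysis.
- If some or all do not, give the confirmed number in both places and add a sentence saying why their one-year data are not usable.

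The cost is one database query, one figure in two places and at most one sentence. No new data and no change of design or model are needed. It should be settled before the tibolone-placebo comparison is reported.
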